### Statistical Procedures

#### Sample Size

The a priori sample size was derived in relation to the primary outcome for this trial, cardiorespiratory fitness assessed at 6 and 12 months. To calculate the sample size, a pooled mean of 20.8 mL/kg/min and a SD of 4.0 mL/kg/min were used based on our previous pilot study [30]. At the time of study design, the meta-analyses of Weston et al [69] reported that supervised HIIT led to approximately twice (approximately 19%) the improvement in VO_2_ peak as compared with MICT (approximately 10%) in participants with lifestyle-induced metabolic disease. We, therefore, used a 9% difference between HIIT and MICT as a meaningful exercise-induced increase in our population of interest, corresponding to a Cohen *d* effect size of 0.48 (or Cohen *f* of 0.24). Using these data, with a two-tailed alpha of .05 and 80% power, assuming a medium correlation among repeated measures of *r*=.5, it is calculated that 15 participants are required per group for a significant within-between interaction (calculated using G*Power v3.1; Department of Psychology, University of Duesseldorf).

However, given that the secondary outcome of exercise adherence typically produces greater measurement variability, the final sample size is determined to be powered for detecting a clinically relevant within-group increase in average daily MVPA assessed by an accelerometer. To calculate sample size, data from the Framingham Heart Study [51] and the Health Survey for England [70] were used. The Framingham data contain the most comprehensive cardiometabolic health measures matched with accelerometry-profiled physical activity in the world (N=2109, mean_age_=47 years, and female=54.53% (1150/2109). Using these data, an increase in 10 minutes of MVPA per day is associated with a 15% reduction in cardiometabolic risk [51]. An increase in approximately 9 min MVPA per day has been shown to reduce progression of prediabetes to T2D [71]. Thus, we calculated sample size to detect a 10-minute increase in average MVPA per day as this amount of activity is linked with improved cardiometabolic health and prevention of T2D. Given that in the Framingham study, the Actical rather than the Actigraph accelerometer was used, additional data were needed from which to derive the mean and SD for MVPA. To this end, the Health Survey for England data were used, which reported an association between physical activity and cardiometabolic risk factors, with MVPA mean values of 12 minutes per day (SD 16). This mean value does not differ markedly from other mean daily MVPA values in either the Canadian Health Measures Survey [72] or National Health and Nutrition Examination Survey [73]. To detect a difference of 10-minutes average MVPA per day within conditions, assuming a SD of 16, with 80% power at *P<*.05, 41 participants per group are required. A conservative loss to follow-up of approximately 20% is anticipated, and therefore, the trial aimed to recruit 50 participants per group (ie, 100 participants to be randomized).

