#### Proposed Data Analyses

Preliminary analyses will be conducted to test for univariate and multivariate outliers and to test for normality. Data transformations will be conducted if required. Variance between the conditions in baseline outcome variables will be examined. Data will be analyzed on an intention-to-treat basis, with individuals retained within their randomized groups regardless of participation. All significance tests will be assessed at a 5% level of significance and effect sizes will be reported. Sensitivity analysis will be conducted to examine the impact of missing data. We will account for missing data by performing multiple imputation by chained equations to determine whether the results are impacted [74].

Mixed-effects regression with baseline as a covariate and 6- and 12-month outcomes as dependent variables will be used to examine differences in cardiorespiratory fitness between HIIT and MICT. Physical activity behavior assessed by accelerometer will be analyzed similarly but will include 3-, 6-, 9-, and 12-month time points. Mixed-effects regression using baseline and all other time points will be used to determine whether the treatments result in a significant change from baseline.

The mediating effects of task self-efficacy, self-regulatory efficacy, concurrent self-regulatory efficacy, outcome expectations, and self-monitoring will be examined using the INDIRECT macro developed by Preacher and Hayes [75]. The macro computes the following steps simultaneously: (1) regression coefficients for the impact of the intervention on the potential mediators; (2) the association between changes in the mediators and changes in the outcome variable; and (3) the total effects, direct effect, and indirect intervention effects. Bias-corrected bootstrapped 95% asymmetrical CIs will be computed for the indirect effect. Significant mediation will be established if the CIs do not include zero. Multiple mediation models will be computed for MVPA at 12-month follow-up and cardiorespiratory fitness at 12-month follow-up.

A series of mixed-effects regressions will be conducted to examine changes over time between groups in anthropometrics, body composition, biochemical markers, CGM, and additional psychological constructs.

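### The figure of 15 per group for 80% power on VO2peak is wrong, because a single-occasion effect size (f = 0.24) was used as a group-by-time interaction effect size

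*Protocol article*

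**What the plan says.** All references are to the protocol article.

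- **Sample Size, inputs.** For VO2peak, "a pooled mean of 20.8 mL/kg/min and a SD of 4.0 mL/kg/min were used". The authors "used a 9% difference between HIIT and MICT as a meaningful exercise-induced increase", which they give as "corresponding to a Cohen *d* effect size of 0.48 (or Cohen *f* of 0.24".
- **Sample Size, result.** The calculation is run "with a two-tailed alpha of .05 and 80% power", "assuming a medium correlation among repeated measures of *r*=.5". Using G*Power, "it is calculated that 15 participants are required per group for a significant within-between interaction".
- **Sample Size, second part.** The final size is set on another outcome, a within-group increase in daily MVPA. That needs 41 per group, raised to 50 per group for about 20% loss.
- **Proposed Data Analyses.** The primary comparison is not an interaction test. It is "Mixed-effects regression with baseline as a covariate and 6- and 12-month outcomes as dependent variables".
- **Primary Outcomes.** VO2peak is measured at baseline, 6 months and 12 months.

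**The concern.** Halving d gives the f for two group means compared at one time point. A within-between interaction measures something else: how far the group difference changes across occasions. In a randomised trial the expected difference is zero at baseline and d at follow-up, so part of d goes into the average group difference and only the remainder is interaction. Using d/2 as the interaction f therefore credits the test with an effect about twice the one stated.

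The number is attached to the primary outcome. A reader learns that 15 per group is enough for VO2peak and that the trial recruits 50 per group only because activity data are noisier. VO2peak then appears to have roughly three times the participants it needs. The powered test also differs from the planned analysis, so the article gives no valid power figure for the primary comparison.

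**Working it through.** **Inputs.** From Sample Size: d = 0.48, SD 4.0, mean 20.8, r = .5, two-sided alpha .05, power 80%. The number of measurements is not stated there. Three is assumed from Primary Outcomes.

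**1. Reproducing 15 per group.** The repeated-measures interaction test with k = 2 groups, m measurements and N participants in total has:

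- noncentrality λ = f²·N·m/(1 − r)
- degrees of freedom (k − 1)(m − 1) and (N − k)(m − 1)

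With f = 0.24, m = 3, r = .5 and N = 30, λ = 0.0576 × 30 × 3 / 0.5 = 10.37 on 2 and 56 df. Power is 80.8%; at N = 28 it is 77.7%. The smallest balanced total is thus 30, or 15 per group, as printed. Two measurements would give N = 38 and four would give N = 26, so only three returns the printed figure.

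**2. The interaction f implied by the stated effect.**

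- Group differences at the three occasions are 0, d, d, with mean 2d/3.
- Deviations from that mean are −2d/3, d/3, d/3. Half of each belongs to each group: d/3, d/6, d/6 in size.
- f² = (d²/9 + d²/36 + d²/36)/3 = d²/18, so f = d√2/6 = 0.2357d.
- For d = 0.48, f = 0.113.

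Then λ at N = 30 is 0.0128 × 30 × 3 / 0.5 = 2.30, against 10.37: a 4.5-fold overstatement. Read backwards, an interaction f of 0.24 needs d = 0.24/0.2357 = 1.02 SD. That is about 4.1 mL/kg/min, or about 20% of 20.8, where the stated target is 9%.

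**3. Power for the planned type of analysis.** After baseline adjustment, the outcome variance in SD² units is:

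- one visit: 1 − r² = 0.75, so the standardised effect is 0.48/√0.75 = 0.554
- mean of two visits: (1 + r)/2 − r² = 0.50, so it is 0.48/√0.50 = 0.679

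Power comes from the noncentral t with noncentrality effect × √(n/2) and 2n − 3 df.

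| Analysis (d = 0.48, r = .5) | Power at 15 per group | n per group for 80% |
|---|---|---|
| Interaction, 3 occasions (f = 0.113) | 24% | 64 |
| Baseline-adjusted, one visit | 31% | 53 |
| Baseline-adjusted, mean of 6 and 12 months | 43% | 36 |

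**4. Sensitivity to r at 15 per group (d = 0.48).**

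| r | Interaction | One visit | Mean of two visits |
|---|---|---|---|
| .5 | 24% | 31% | 43% |
| .7 | 38% | 43% | 56% |
| .8 | 54% | 56% | 70% |
| .9 | 85% | 83% | 92% |

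**5. Power at the planned size.** A 20% loss from 50 leaves 40 per group; the MVPA calculation asks for 41. The range for d covers 0.09 × 20.8/4.0 = 0.468 and the printed 0.48. With r = .5:

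- mean of 6 and 12 months, baseline-adjusted: 83-86%
- one visit, baseline-adjusted: 67-70%
- three-occasion interaction: 56-60%

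**The case against.** The strongest reply is that nothing in the design depends on the 15. The size was set at 50 per group on MVPA, and the planned baseline-adjusted model then exceeds 80% power for the difference averaged over both visits. That is right, and it limits the point to a wrong supporting figure.

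Second, the lowest power (24%) belongs to the interaction test, which is not the planned analysis. That is also fair, although it is the test the article names. For the planned kind of model the figures at 15 per group are 31% and 43%, still far from 80%.

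Third, the percentages depend on r = .5, which the article assumes and does not estimate. A higher correlation would raise them, but 15 per group still misses 80% at r = .7 and r = .8. Only a value near .9 would rescue it.

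Two stronger readings should be resisted.

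- A reader might infer that a null 12-month result is bound to be over-read because power there is only 67-70%. The article puts 6 and 12 months in one model and does not make 12 months alone decisive. At r = .7 the single-visit power at 40 to 41 per group is already about 83-85%.
- A reader might count 0.468 against the printed 0.48 as a second error. The underlying improvements are given only as approximate percentages, so the gap is within rounding, and it moves power by about two points.

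The 9% does come from supervised training, while follow-up here is independent exercise. How much of the effect would persist is a separate question, and the article gives no figure for it.

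**Conclusion.** The statement that 15 per group gives 80% power for VO2peak is wrong on the article's own inputs. Converting d to f by halving is correct in itself; the error is using that f for the interaction. The effect size is overstated about 2.1-fold and the noncentrality about 4.5-fold. Under r = .5, true power at 15 per group is between 24% and 43%, depending on the analysis, and 36 to 64 per group are needed.

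This rests on no expected baseline difference, the same difference at 6 and 12 months, r = .5 between all pairs of occasions, and three measurements. The last is inferred, but it is the only one of the counts tried (two, three, four) that returns the printed number.

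It would be tempting to conclude that the trial is underpowered for its primary outcome. The documents do not support that: at the planned size the averaged baseline-adjusted comparison has about 83-86% power. What falls away is the impression of a large reserve.

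**What to change.** Correct or withdraw the figure of 15 per group in Sample Size. Data collection is already complete, so a marked correction that leaves the historical calculation visible is better than silent deletion.

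In its place, state power for the analysis in Proposed Data Analyses at the planned size. For a 9% difference (d = 0.47 to 0.48), r = .5 and 40 to 41 completers per group, the baseline-adjusted model has about 83-86% power for the HIIT-MICT difference averaged over 6 and 12 months, and about 67-70% at a single visit. State that both figures depend on the assumed correlation.

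The cost is one recalculation and a few sentences. No change to recruitment or to the analysis model is needed. The stated position for the primary outcome becomes less favourable, but it will match the planned analysis.

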#### Proposed Data Analyses

Preliminary analyses will be conducted to test for univariate and multivariate outliers and to test for normality. Data transformations will be conducted if required. Variance between the conditions in baseline outcome variables will be examined. Data will be analyzed on an intention-to-treat basis, with individuals retained within their randomized groups regardless of participation. All significance tests will be assessed at a 5% level of significance and effect sizes will be reported. Sensitivity analysis will be conducted to examine the impact of missing data. We will account for missing data by performing multiple imputation by chained equations to determine whether the results are impacted [74].

Mixed-effects regression with baseline as a covariate and 6- and 12-month outcomes as dependent variables will be used to examine differences in cardiorespiratory fitness between HIIT and MICT. Physical activity behavior assessed by accelerometer will be analyzed similarly but will include 3-, 6-, 9-, and 12-month time points. Mixed-effects regression using baseline and all other time points will be used to determine whether the treatments result in a significant change from baseline.

The mediating effects of task self-efficacy, self-regulatory efficacy, concurrent self-regulatory efficacy, outcome expectations, and self-monitoring will be examined using the INDIRECT macro developed by Preacher and Hayes [75]. The macro computes the following steps simultaneously: (1) regression coefficients for the impact of the intervention on the potential mediators; (2) the association between changes in the mediators and changes in the outcome variable; and (3) the total effects, direct effect, and indirect intervention effects. Bias-corrected bootstrapped 95% asymmetrical CIs will be computed for the indirect effect. Significant mediation will be established if the CIs do not include zero. Multiple mediation models will be computed for MVPA at 12-month follow-up and cardiorespiratory fitness at 12-month follow-up.

A series of mixed-effects regressions will be conducted to examine changes over time between groups in anthropometrics, body composition, biochemical markers, CGM, and additional psychological constructs.

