**Methods:**

Small Steps for Big Changes is a 2-arm randomized controlled trial that will examine the effectiveness of combining brief exercise counseling with HIIT or MICT on adherence to moderate and vigorous exercise over 1 year. Cardiorespiratory fitness will be assessed at baseline, post intervention (2 weeks), and at 6- and 12-month follow-up. Physical activity behavior will be examined at baseline, post intervention, and 3-, 6-, 9-, and 12-month follow-up. The impact of the intervention on psychosocial outcomes pertinent to exercise adherence will be examined.

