#### Primary Outcomes

The primary outcome is cardiorespiratory fitness determined by measuring VO_2_ peak at 6- and 12 months postrandomization. VO_2_ peak will be assessed by a continuous incremental ramp maximal exercise test on an electronically braked cycle ergometer (Lode Excalibur, The Netherlands). Expired gas will be collected continuously by a metabolic cart (Parvomedics TrueOne 2400, Salt Lake City, Utah, USA) that is calibrated with gases of known concentration and a 3.0 L syringe before every test. The test begins with a 4-minute warmup at 30 Watts, after which Watts increase by 1 every 4 seconds (15 Watts per minute). Verbal encouragement will be provided to the participant throughout the test. The test will be terminated upon volitional exhaustion or when revolutions per minute fall below 50. VO_2_ peak is defined as the highest 30-second average for VO_2_ (in L/min and mL/kg/min). Criteria for achieving VO_2_ peak are (1) respiratory exchange ratio >1.15; (2) plateau in VO_2_; (3) reaching age-predicted heart rate (HR) peak (220-age); and/or (4) volitional exhaustion. A Polar chest strap, which is integrated with the metabolic cart and cycle ergometer software (Lode Exercise Manager), will capture HR. HR peak and peak power output will be recorded as the highest values attained in the test. Cardiorespiratory fitness will be assessed at baseline and 6- and 12-month follow-up.

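### The between-arm fitness model conditions on no 2-week response, and the protocol disagrees with itself on whether a 2-week value exists: reconcile the schedule and, if the value was collected, add it to the model

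*Protocol article*

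**What the plan says.** **Model.** Proposed Data Analyses fixes the arm comparison: "Mixed-effects regression with baseline as a covariate and 6- and 12-month outcomes as dependent variables will be used to examine differences in cardiorespiratory fitness". Accelerometer activity is treated alike, with the 3-, 6-, 9- and 12-month values as outcomes. A second mixed model, using baseline and every other time point, is described for change from baseline and not for the arm contrast.

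**Endpoint.** "The primary outcome is cardiorespiratory fitness determined by measuring VO_2_ peak at 6- and 12 months postrandomization".

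**Missing data.** Sample Size states: "A conservative loss to follow-up of approximately 20% is anticipated". Proposed Data Analyses says "Data will be analyzed on an intention-to-treat basis, with individuals retained within their randomized groups regardless of participation" and adds a sensitivity analysis: "We will account for missing data by performing multiple imputation by chained equations to determine whether the results are impacted".

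**Schedule.** The abstract says "Cardiorespiratory fitness will be assessed at baseline, post intervention (2 weeks), and at 6- and 12-month follow-up", and it also lists activity after the intervention. Primary Outcomes says "Cardiorespiratory fitness will be assessed at baseline and 6- and 12-month follow-up". The Physical Activity section schedules accelerometry at baseline and at 3, 6, 9 and 12 months. The objectives name only 6 and 12 months for fitness and 3 to 12 months for activity.

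**The concern.** A likelihood-based mixed model protects against dropout that depends on earlier outcomes only when those outcomes are in the model. Here the only earlier value is baseline. Someone who finishes the supervised two weeks and then gives neither a 6- nor a 12-month value has no dependent variable and does not enter the estimate. Nothing observed at the end of the supervised phase is used to judge how such people differ from those who stay.

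Participants know their allocation, and the trial itself sets out to compare affect, enjoyment and exertion between the two modalities. It is therefore conceivable that early response drives loss differently in HIIT and MICT. If so, the primary contrast moves, although a 2-week value in the same model would absorb the effect.

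**Working it through.** **1. The plan's own figure.** Sample Size gives 15 per group for the within-between interaction with f = 0.24, r = .5, two-sided alpha .05 and 80% power. With noncentrality λ = f²·N·m/(1−r) and degrees of freedom (m−1) and (N−2)(m−1):

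| Measurements m | Total N | Per group | Power |
|---|---|---|---|
| 2 | 38 | 19 | 0.821 |
| 3 | 30 | 15 | 0.808 |
| 4 | 26 | 13 | 0.817 |

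For m = 3, λ = 0.0576 × 30 × 3 / 0.5 = 10.37. The stated 15 fits three measurements (baseline, 6 and 12 months). It agrees with the schedule without a 2-week test but does not prove it.

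**2. The schedule side by side.**

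| Place | Fitness at 2 weeks | Activity at 2 weeks |
|---|---|---|
| Abstract, Methods | yes | yes |
| Objectives | not listed | not listed |
| Primary Outcomes / Physical Activity | not listed | not listed |

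**3. Inputs for the size.** From Sample Size: 50 per arm, 20% loss (about 10 per arm), SD 4.0, mean 20.8, target difference 0.09 × 20.8 = 1.87 mL/kg/min, r = .5. Assumed: r = .8 as an alternative, compound symmetry, all loss between week 2 and month 6, and log-odds of dropout changing by 1 per SD of the 2-week change in fitness.

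**4. Formula for one arm.** Let σ = 4.0. The 2-week change has SD σ√(2(1−r)). With slope 1 and 20% lost, numerical integration puts the completers' mean change 0.173 SD away from that of everyone randomised; call this shift δ = 0.173·σ√(2(1−r)).

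- Half of δ falls on the 2-week value and half, with opposite sign, on baseline.
- Adjusting for baseline (slope r) leaves ½δ(1+r) on the 2-week value.
- Given baseline, a later value follows the 2-week value with coefficient r/(1+r).
- The shift in the later mean is the product, ½·δ·r = 0.173·σ·r·√(2(1−r))/2.

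At r = .5: 0.173 × 4 × 0.5 × 1 / 2 = 0.17. At r = .8: 0.173 × 4 × 0.8 × 0.632 / 2 = 0.17 to 0.18. If the slopes run in opposite directions in the two arms, the shift doubles to about 0.35. If they are the same, it cancels.

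**5. Simulation, all loss before month 6 (true value 1.87).**

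| Dropout depends on 2-week change | Planned model | With 2-week value added |
|---|---|---|
| Equally in both arms | 1.87 | 1.87 |
| In one arm only | 1.70 (−9%) | 1.87 |
| In opposite directions | 1.51 (−19%) | 1.87 |
| One arm only, sign reversed | 2.04 | 1.87 |
| Opposite directions, signs reversed | 2.22 to 2.23 | 1.87 |

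The results at r = .8 agree to within about 0.01. The largest deviation at this slope is 0.36.

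**6. Later loss.** If half the loss comes after month 6 (r = .5), those participants contribute their 6-month value. The average of the two visit contrasts is then 1.76 (−6%) for one arm only and about 1.64 to 1.65 (−12%) for opposite directions.

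**7. Against the noise.** With 40 per arm observed, the variance of the 6- and 12-month mean given baseline is 16 × (0.75 − 0.25) = 8, so SE = √(8 × 2/40) = 0.63. The deviation is 0.17/0.63 = 0.27 to 0.36/0.63 = 0.57 of one standard error. Adding the 2-week value leaves the SE at 0.63 to 0.64.

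**The case against.** Four points can fairly be made for the plan as written.

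- **The model matches the endpoint.** A baseline-adjusted mixed model on exactly the 6- and 12-month visits is a standard choice for an outcome defined at those visits, and a participant with only one of the two still contributes. This stands: the restriction is not an error in itself.
- **A 2-week value may not exist.** A reader might infer that the plan discards a fitness test it has in hand. The documents do not support that. Only the abstract lists the test; the detailed sections omit it, and the sample size reproduces without it.
- **Missing data are addressed.** Chained-equations imputation can bring back participants without follow-up and can draw on any 2-week data. This softens the point. It does not remove it, because imputation is a sensitivity analysis and the primary estimate stays as specified. Which variables enter it can properly be left to an analysis plan.
- **Intention to treat is not broken.** A reader might infer a broken promise when people without outcomes drop out of the model. In its ordinary sense, the sentence promises analysis as randomised whatever the adherence, not a contribution from everyone.

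A reader might also infer that any dropout linked to early response biases the contrast. It does not: an equal link in both arms gave no bias. Nothing in the documents shows that the link differs by arm, or when the loss occurs.

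**Conclusion.** The point holds as a modest, conditional improvement. As specified, the arm comparison takes nothing from participants without a later value and conditions on no 2-week response. If dropout depends on early response differently by arm, the contrast is off by about 0.17 to 0.36 mL/kg/min on 1.87, in either direction, with all 20% lost before month 6, and by less with later loss. That is roughly a quarter to just over half of one standard error. The dropout slope, its difference between arms, the timing of loss and the covariance structure are assumptions; the documents supply only the 20%, the SD, r = .5 and the target difference. No size was worked out for activity, where the same reasoning applies. The disagreement between the abstract and the outcome sections is in the text itself and needs no assumption.

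**What to change.** 1. Reconcile the abstract with Primary Outcomes and Physical Activity, and state whether fitness and accelerometry were measured at 2 weeks.
2. If they were, add the 2-week value as a further dependent variable in the between-arm model, with baseline as covariate, visit, arm, arm-by-visit and an unstructured covariance. Keep the 6- and 12-month arm contrasts as the primary result; because arm-by-visit is free, the 2-week effect does not dilute them. Treat activity the same way, with 2 weeks added to 3 to 12 months.
3. If they were not, name the post-intervention measures that are scheduled or recorded (body mass, efficacy scales, enjoyment, session attendance) as auxiliary variables in the planned imputation, and report that result beside the primary one.

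The cost is analysis wording only: no new data, unchanged primary contrasts and practically the same standard error. Since the Results section says that analysis is under way, date the change and record whether it was made before any arm comparison was seen.
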